## Abstract

**Background:**

Limb injuries comprise 50-60% of U.S. Service member’s casualties of wars in Afghanistan and Iraq. Combat-related vascular injuries are present in 12% of this cohort, a rate 5 times higher than in prior wars. Improvements in medical and surgical trauma care, including initial in-theatre limb salvage approaches (IILS) have resulted in improved survival and fewer amputations, however, the long-term outcomes such as morbidity, functional decline, and risk for late amputation of salvaged limbs using current process of care have not been studied. The long-term care of these injured warfighters poses a significant challenge to the Department of Defense (DoD) and Department of Veterans Affairs (VA).

**Methods/Design:**

The VA Vascular Injury Study (VAVIS): VA-DoD Extremity Injury Outcomes Collaborative, funded by the VA, Health Services Research and Development Service, is a longitudinal cohort study of Veterans with vascular extremity injuries. Enrollment will begin April, 2015 and continue for 3 years. Individuals with a validated extremity vascular injury in the Department of Defense Trauma Registry will be contacted and will complete a set of validated demographic, social, behavioral, and functional status measures during interview and online/ mailed survey. Primary outcome measures will: 1) Compare injury, demographic and geospatial characteristics of patients with IILS and identify late vascular surgery related limb complications and health care utilization in Veterans receiving VA vs. non-VA care, 2) Characterize the preventive services received by individuals with vascular repair and related outcomes, and 3) Describe patient-reported functional outcomes in Veterans with traumatic vascular limb injuries.

**Discussion:**

This study will provide key information about the current process of care for Active Duty Service members and Veterans with polytrauma/vascular injuries at risk for persistent morbidity and late amputation. The results of this study will be the first step for clinicians in VA and military settings to generate evidence-based treatment and care approaches to these injuries. It will identify areas where rehabilitation medicine and vascular specialty care or telehealth options are needed to allow for better planning, resource utilization, and improved DoD-to-VA care transitions.

## Background

### Combat-related vascular injuries

Wartime injuries have been studied during every major conflict of the 20^th^ and 21^st^ centuries. Hughes in Korea [1], and Rich in Vietnam [2], each advanced the care of Service members with vascular injuries. Ligation of injured blood vessels and the resultant high limb loss rate in World War II gave way to arterial and venous repair in the Korean and Vietnam Wars. With these advances, life and limb salvage rates improved dramatically in the short and mid-term time frame. However, long term outcomes following the definitive repair of wartime vascular injuries by a vascular specialist in the theater of war have not previously been evaluated. *To improve care, we must provide long term follow up and define the natural history of wartime vascular injury over an injured Soldier’s lifetime.*

Improvements in battlefield protection devices, casualty evacuation and medical care have enhanced survival rates, currently over 90%, following combat injuries. Many survivors of once-lethal injuries now require prolonged medical and rehabilitation care for polytrauma injuries [3]. Rapid aero-medical evacuation from the battlefield to definitive surgical care has been a major contributor to improved initial limb salvage rates, allowing access to vascular surgery care more rapidly, thereby decreasing ischemia times of injured limbs. The in-theatre use of diagnostic angiography and endovascular treatments has enabled more attempts at limb salvage after extremity vascular injury [4]. Additionally, patients usually leave the theater of war within 24 hours after receiving initial medical treatment [4–6]. Subsequent care is obtained in several locations while en route to the United States, and in military trauma centers in the U.S. Once the acute hospitalization phase is completed, and longer term rehabilitation at Walter Reed National Military Medical Center or the San Antonio Military Medical Center is completed, the patient will be released to the home station and the associated military treatment facility (MTF) or to the local community. In the event that the Service member separates from the DoD, care is often transferred to the Veterans Administration (VA), especially when high service-connected ratings of disability are present. Most of the MTFs do not have a vascular surgeon or non-invasive vascular laboratory (duplex ultrasound) to provide long-term surveillance of the vascular repair.

### Prospective and retrospective studies of orthopaedic and vascular injury are limited

The Lower Extremity Assessment Project (LEAP) was a prospective, longitudinal study performed at 8 level 1 civilian trauma centers to study the outcomes of lower extremity orthopaedic trauma to answer the questions surrounding the decision to amputate or salvage injured limbs [7]. While there were no controls for the therapeutic interventions, long-term follow up of 7 years is available on most patients. The results of multiple studies emanating from this trial are reviewed in Higgins *et al*. [7] Major findings include similar self-reported health status measures 2 years after injury in patients undergoing amputation compared to limb reconstruction. However, patients with limb reconstruction had a higher rate of complications and rehospitalization [8]. While two year health care costs were similar between patients with limb salvage and amputation, prosthesis-related expenses increased the costs for patients with amputations and the projected lifetime health care costs were three times higher for patients with amputation compared to limb salvage [9]. None of the lower extremity injury severity indices have been shown to be sensitive predictors of which patients should undergo initial amputation versus limb reconstruction [7]. The only study that focused on vascular injuries was in association with knee dislocation; this study contained 18 patients and suggested that outcomes in revascularized patients were better than those undergoing amputation [10].

The Military Extremity Trauma Amputation/Limb Salvage (METALS) study applied methods similar to those in the LEAP study to the Operation Enduring Freedom/Operation Iraqi Freedom/Operation New Dawn (OEF/OIF/OND) military population [11]. This retrospective cross-sectional study included 324 U.S. Service members who had sustained major lower limb trauma as a result of high-energy blast and ordnance-related mechanisms. Both unilateral and bilateral lower limb traumatic injuries were included. Clinical data were obtained from participants’ medical records and through telephone interviews. Patients in the limb salvage and amputation groups reported significant disability compared to normal populations and 38% screened positive for depressive symptoms with 34% not working or in school at the time of the interview. Of interest, amputees reported better scores on the SMFA compared to limb reconstruction patients as well as lower rates of post-traumatic stress disorder. Only 17 limb salvage patients (~10%) in the study underwent revascularization [11]. These findings are in contrast to LEAP which reported similar health status measures in amputees and limb salvage patients, suggesting that translation of findings from non-combat civilian settings to combat injury may not be generalizable.

The Late Amputation Study Team (LAST) was to determine the prevalence of late amputations in wounded Service members from OEF/OIF/OND. While most amputations occurred in the acute setting, 15% of Service members sustaining lower extremity injuries had late amputations, defined as greater than 12 weeks after injury, range 12 weeks to 5.5 years [12]. A subset of these patients with type III open diaphyseal tibia fractures managed with late amputation were shown to have an increased incidence of infection [13].

### Studies examining long term outcomes associated with vascular interventions are limited

In the Global War on Terror Vascular Initiative (GWOT VI) Rasmussen and colleagues defined the patterns and types of injuries [5, 14] as well as short term outcomes of using temporary vascular shunts [6], efficacy of incorporating endovascular procedures [4], and selective repair of tibial artery injuries [15]. OEF/OIF/OND vascular trauma occurred at a 5-times higher rate than previous wars and was caused predominantly by explosive (73%) and gunshot (27%) injuries [5]. The increased vascular trauma rate may be attributable to improvements in body armor, and increased survivability due to the use of tourniquets and shorter casualty evacuation times [5]. As a follow up to the acute care studies, the DoD team initiated a survey study using the SF-36®, SMFA and a questionnaire to determine the functional outcomes of Service members with extremity vascular injury repairs [16]. Long-term outcomes assessment for this study was limited by the inability of the DoD team to access VA databases.

Similar to military trauma, multiple reports document the acute care of patients with civilian vascular extremity injuries, but limited data on small sample sizes is available for long-term outcomes [17]. Thirteen of 22 patients were available with a mean follow-up of 59 months demonstrating graft patency by duplex ultrasound [17]. Additional studies [18–20] on small numbers of patients with long term follow up used ankle-brachial indices or clinical evaluation, which are often inaccurate methods to assess graft patency [21].

What we know about long-term treatment for patients following vascular repair is based on vascular repair due to atherosclerotic disease. Evidence-based treatments recommended in this patient population include antiplatelet therapy and *duplex ultrasound graft surveillance.* Antiplatelet therapy, especially aspirin, is considered standard of care for patients with atherosclerotic disease to prevent death and disability from stroke and myocardial infarction. Aspirin doses of 80 to 325 mg/day are effective compared to higher-dose aspirin which can increase side effects [22]. Multiple studies and reviews have concentrated on drug therapies to increase patency rates in extremity vascular bypasses, all focusing on patients with atherosclerosis. The Antiplatelet Trialists’ Collaboration found that antiplatelet therapy was associated with a relative risk reduction of 43% in graft occlusion [23]. However, the optimal therapies that maximize graft patency and minimize complications may vary depending on a variety of factors, including whether a venous or prosthetic graft is used. The Dutch Bypass Oral Anticoagulant study (BOA) compared vitamin K antagonists to aspirin and determined that vitamin K antagonists were more beneficial in patients with vein grafts, albeit with a higher rate of major bleeding episodes, while aspirin improved patency in prosthetic grafts [24]. Possible explanations for these observations include that aspirin may decrease platelet deposition on the more thrombogenic surface of prosthetic grafts while the coagulation cascade may be more critical in vein graft occlusions [25]. Despite the BOA study, the Seventh American College of Chest Physicians Conference on Antithrombotic and Thrombolytic Therapy evidence-based guidelines recommended using aspirin, rather than vitamin K antagonists, in both venous and prosthetic bypass grafts and the combination of aspirin plus vitamin K antagonists for patients with a high risk of graft thrombosis and limb loss, noting that the recommendations placed a high value on the avoidance of bleeding complications [22]. A Cochrane review for preventing thrombosis after arterial surgery concluded that limited evidence suggested antiplatelet agents such as aspirin, pentoxifylline, or aspirin given with dipyridamol improved graft patency compared to no treatment. However, patients with prosthetic grafts benefited more from aspirin or aspirin given with dipyridamol than patients with venous grafts. For venous grafts, vitamin K antagonists may be more beneficial and a combination of aspirin and clopidogrel might be as effective as vitamin K antagonists [26]. These observations led to the Clopidogrel and Acetylsalicylic acid in bypass Surgery for Peripheral Artery disease (CASPAR) trial comparing aspirin plus clopidogrel to aspirin alone in patients undergoing below the knee bypasses for peripheral arterial disease. In the overall population, graft patency was similar in patients receiving aspirin plus clopidogrel compared to aspirin alone. However, subgroup analysis revealed an increased graft patency for aspirin plus clopidogrel in patients receiving prosthetic grafts without increasing major bleeding complications [25]. Finally, a systematic review of endovascular therapies found evidence to support the recommendation of aspirin 50 to 300 mg with clopidogrel possibly being an alternate therapy [27].

Statin use has been associated with increased cardiovascular graft patency, see [28] for recent review. While statins were associated with improved 1 year survival in patients receiving lower extremity grafts for atherosclerotic disease, graft patency was not affected by statin use [29]. Statin use and graft patency remains an open critical question; especially given adverse effects (e.g. myopathy) associated with statin use [30].

*Duplex ultrasound graft surveillance* is the standard of care for monitoring bypass grafts and vascular interventions including vein grafts, angioplasties and/or stents [21, 31–34]. This technique allows the physician to visualize the structure of the blood vessels, how blood is flowing through the vessels and measures the speed of the flow of blood. Duplex ultrasound can also be useful to estimate the diameter of a blood vessel/graft as well as determine if a stenosis/occlusion has occurred. This application has been extensively studied in patients with atherosclerosis as the etiology for requiring intervention [21, 31–34]. However, support for use of duplex ultrasound after vascular interventions performed following traumatic injury is limited [17]. *No information is available regarding the extent to which this standard of care is met either in the VA or DoD for vascular repairs performed in trauma patients.*

In summary, antiplatelet agents are a mainstay in the treatment of patients after bypass and endovascular therapies for atherosclerotic disease secondary to their salutary role in decreasing cardiovascular events and maintaining graft/endovascular repair patency. Exclusion criteria for randomized control trials often exclude patients with risk factors for bleeding; thus, the incidence of complications in the general population with these treatments may be different than in the trials. Statin use has been advocated to improve vascular graft patency; however, prescription patterns in Veterans with vascular repairs for trauma are unknown. Duplex ultrasound graft surveillance has also been used extensively in patients undergoing vascular repair for atherosclerosis to detect graft failure. Finally, studies in atherosclerotic patients may not translate to the predominately younger trauma population and the etiology of graft failure may be different in trauma patients. Thus, understanding treatment practices of prescribing antiplatelet agents and other anticoagulants, and the associated complications with these treatments, as well the role of duplex ultrasound, will be a first step in defining the care of Veterans and civilians with extremity vascular trauma.

### Aims of the VA Vascular Injury Study (VAVIS)

VAVIS is a longitudinal cohort study designed to examine outcomes associated with in-theatre vascular injury, funded by the Department of Veterans Affairs (VA), Health Services Research and Development Service. Figure 1 shows the theoretical model that guides our research. This model posits that understanding the health care delivery process for these injuries will result in a better understanding of their outcomes. Therefore, the goal of VAVIS is to characterize patients with initial in-theatre limb salvage (IILS) and identify late vascular surgery related limb complications in Veterans receiving VA vs. non-VA care.

**Figure 1 Fig1:**
[figure not shown]
**Donabedian’s model of quality of care posits that processes of care (Vascular Preventive Care) may be associated with patient outcomes.** However, the complex relationships among demographic characteristics, initial injury severity, and comorbid physical and psychiatric conditions require careful attention to the potential for confounding and effect modifiers. While it is also important to control for demographic characteristics, particular concern is focused on controlling for disease burden and initial injury characteristics since these may have substantial impact on the outcome that is unrelated to the initial vascular injury and preventive care.

Because little is known about the natural history of these types of injuries given modern combat casualty care, our first aim is to describe the population of interest including initial and subsequent treatment in the DoD. Our second aim is to describe extant preventive care processes provided for individuals with IILS by the VA since best practices for individuals with traumatic vascular repair have not been established and little is known about the types of preventive care available. Because research in other types of care have found that processes of care identified as best practices are associated with patient outcomes [35], our third aim is to identify the association of Vascular Preventive Care with patient outcomes [36] such as measures of persistent morbidity, adjusting for potential confounders, and effect modifiers. While it is also important to control for demographic characteristics, particular concern will be focused on controlling for traumatic brain injury, physical and psychiatric disease burden, and initial injury characteristics since these may have substantial impact on the outcome that is unrelated to the initial vascular injury and preventive care [37]. If Vascular Preventive Care processes are associated with positive patient outcomes, there will be support for these care processes as best practices [38].

Our fourth aim is to describe long-term patient-reported outcomes in Veterans with traumatic vascular limb injuries controlling for potential confounders such as complexity of the combat injury (i.e., involvement of neurological and musculoskeletal components), traumatic brain injury, and comorbid mental and physical health conditions. Improvements in battlefield care, such as the use of temporary vascular shunts, transfusion methods, *etc.*, have evolved at a very rapid pace, but there is a need to understand the long-term outcomes of these treatments to inform clinical decision making and thus fully optimize trauma systems fielded in-theater. Findings from VAVIS will provide insight for military trauma, vascular and orthopedic surgeons to know which types of injuries can be repaired with adequate functional outcome to justify the initial surgical decision. It can be a particularly traumatic and demoralizing experience for a patient to undergo multiple procedures to attempt limb salvage only to lose the limb later due to ischemia, infection, extensive musculoskeletal injury or pain. A better understanding of outcomes will identify which patients may benefit from initial amputation versus attempts at vascular repair.

## Methods/Design

This observational cohort study of Veterans who receive VA care for IILS will use retrospective data from the DoD and VA that was collected for the GWOT VI study (DoD) and the Trajectories of Resilience and Complex Comorbidity (TRACC [VA]) studies in addition to interview and survey data collected during the course of this study.

### Study sample

Our denominator includes all individuals verified as having undergone initial in-theatre limb salvage (IILS) during the GWOT VI study. Inclusion criteria for IILS included: 1) received a vascular repair on the affected limb(s) and 2) transferred to the post-anesthesia unit and to the ICU after surgery. Individuals with amputations performed as the first, in-theatre operation are excluded.

To date, DoD chart abstractions using the Department of Defense Trauma Registry (DoDTR) have identified 1,363 individuals with confirmed extremity vascular injury and initial limb salvage; approximately 1,266 of these have separated from active service (Figure 2). Based on VA enrollment data, approximately 59% of OEF/OIF/OND Veterans discharged from the military have received VA health care [39], we expect approximately 700 individuals in the VA denominator. Database and chart abstraction components will include all those who received VA care (estimated N = 700). Additional analyses will be conducted for those who do not receive VA care within limits of available data.

**Figure 2 Fig2:**
[figure not shown]
**Eligibility flow diagram showing DoD chart abstractions using the Department of Defense Trauma Registry (DoDTR).**

### Study procedures

The VAVIS protocol was reviewed and approved by the VA Central IRB. This three component study will begin first by compiling data previously collected from DoD and VA (FY01-FY14), linking files from each source using the unique identifier. Once VA patients in the confirmed IILS cohort are identified, we will conduct medical chart abstraction of VA electronic medical records, and conduct a patient interview and survey to obtain patient reported outcomes. The study will start on April 1, 2015 and will be open for three years.

### Previously collected data

Data abstracted from the DoD medical chart in the GWOT VI study will be used in this study as control variables, or characteristics for stratification based on expert consensus of our clinical team. Table 1 provides a description of the type of information included in the GWOT VI dataset. These DoD data will be merged with national VA health care system data collected as part of the TRACC study (VA inpatient, outpatient, pharmacy and non-VA care [Fee Basis/ Medicare] data). Table 2 provides a description of the variables, definitions and data sources used to create variables. For those who have received VA or Medicare care, we will develop variables related to indicators of persistent morbidity, type of care received, and long-term outcomes. Table 3 provides a specific description of these measures and how they are defined.

**Table 1 Tab1:** **Information obtained from DoD chart abstraction: baseline polytrauma injury characteristics**

Type of variable	Information
Demographics	Age, sex, race/ethnicity and service branch
Initial Injury Information	Date, primary cause/mechanism
Vascular Extremity Details	Arterial/venous injury location, pre/post repair details, and complications.
Ortho/Nerve Extremity Details	Associated soft tissue/bone/nerve injuries, methods of repair, flap status.
Follow Up Care	Dates, location, and CT/MRI/Angio/Duplex studies.
Functional/ Amputation status	Limitations, context of amputation if relevant

**Table 2 Tab2:** **Data variables, definitions, and data sources**

Variables	How defined	Data source
**Demographic Characteristics**	Age, Sex, Race/ Ethnicity, Education	OEF/OIF/OND Roster File (from Environmental Epidemiology Service)
**Military Characteristics**	Rank, Component (active, guard, reserve), Service Branch,	
**Military Discharge Date**	Military discharge dates	
**Other Demographic Characteristics**	Marital status	National VA Inpatient and Outpatient Care Files (Medical SAS data sets)
**Diagnoses** for which care is received	ICD-9-CM Codes each visit	
**Location of Care/ Facility Type** (e.g. Medical Center, outpatient clinic, community based outpatient clinic)	STA5A/STA6A; Last letter of code indicates the type of facility	
**Type of care**: Relevant specialty care: vascular surgery clinic (415), vascular lab (421), amputation clinic (418), prosthetic clinic (417), PM&R (201,211).	DSS Identifier (stop code)	
**Procedures:** tests such as duplex ultrasound or type of surgery when admission is on day of surgery	CPT-4 Codes	
**Geospatial data** of patient home to identify distance to primary station and clustering of these Veterans across the country.	Zip Code, Longitude/latitude of patient residence	
**Diagnoses** for which care is received	ICD-9-CM Codes each visit	National VA Inpatient Care Files (Medical SAS data sets from national repository at the Austin Automation Center)
**Location of Care/ Facility Type** (e.g. Medical Center, domiciliary, neuro/psychiatric hospital)	STA5A	
**Provider Specialty**: Bedsection is mapped 1:1 with provider specialty (e.g., vascular [106] and peripheral vascular [62].	Bedsection	
**Procedures:** tests such as duplex ultrasound or type of surgery	ICD-9A Codes	
**Geospatial** (same as above)	Zip Code, Longitude/latitude patient home	
**Medications Prescribed** (e.g., opioids, other medications for pain, antibiotics for persistent infections such as osteomyelitis, antiplatelet agents, statins)	VA Product name, strength, day supply, number of pills dispensed Medicare Part D National Drug Code (NDC)	National Pharmacy Files from the Pharmacy Benefits Management Strategic health Group, Medicare Part D
**Dose** of medications average monthly dose (dose per unit × day supply)	Generic, day supply, number of units, dose, Medicare Part D: NDC code	
**Duration** of use	Day supply summed over time	
Specific Prosthetic Device	HCPCS PSAS, HCPCS CPT codes identify the specific item	National Prosthetics Patient Database (NPPD)
Specific Service Connected Disability and % disability for each condition	VETSNET condition code, %, number of disabling condition, service connected disability indicator	Veterans Service Network (VETSNET) Corporate Mini Master File (VETSNET File) derived from the Veterans Benefits Administration (VBA) Corporate Database.
Pain Scores: longitudinally (1–10 each visit)	Pain score	Corporate Data Warehouse

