**Table 3 Tab3:** **Indicators of persistent morbidity**

Indicators of persistent morbidity	Data used to identify	Data source
Use of unscheduled or emergency care for vascular issues	DSS Clinic Identifier and ICD-9 Codes	Outpatient (OPC) files; VA-CMS
Use of scheduled care for polytrauma vascular issues	DSS Clinic Identifier and ICD-9 Codes	OPC files; VA-CMS
Long-term use/escalating dose of opioid medications	VA Product, Dose, Day Supply	Pharmacy Benefits Management (PBM) Data; Medicare Part D VA-CMS
	NDC Code	
Trajectory of chronic pain (latent class analysis of pain scores from TRACC)	Pain Score	CDW vitals
Conditions indicative of persistent morbidity (e.g., Venous stasis disease/venous ulcers, lymphedema)	ICD-9 Codes including but not limited to 729.81, 782.3, 729.5, 415.19, 451.11, 451.19 451.83, 451.82, V72.83	PTF, OPC files, VA-CMS
Prescriptions for compression stockings and wound care supplies (e.g., wound vac) indicative of swelling, venous stasis disease	VA Class	PBM Data, VA-CMS Durable Medical Equipment
	XA	
Use of prosthetic/orthotic devices (canes, walkers, special shoes, etc).	Health Care Financing Administration Coding System (HCPCS) Prosthetic and Sensory Aids Service (PSAS) Code;	National Prosthetics database
		CMS Durable Medical Equipment
Additional procedures (open or endovascular) on the injured extremity	CPT-4; ICD-9A procedure codes	OPC/PTF VA-CMS
Chronic antibody use (osteo or other potential infectious issues with the limb)	VA Product	PBM Data; Medicare Part D VA-CMS
Duplex ultrasound, MRA/CTA or angiogram to evaluate the repair	CPT-4 procedure codes including but not limited to 93970, 93971, 93975, 93976, 93978, 93979, 93922, 93923, 93925, 93926, 93930, 93931, 93924	OPC/PTF; VA-CMS
Mean pain scores over 4	Pain Score Mean per year	Corporate data warehouse Vital Signs
Proportion of VA care	Visits VA/ Total Visits	OPC/PTF; VA CMS outpatient/inpatient
Mortality	Date of Death	VA Vital Status file

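### The Table 2 expression for average monthly dose leaves out units dispensed and has no monthly scaling, so opioid dose escalation would be misclassified if Table 3 uses it

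*Protocol article*

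**What the plan says.** The section Previously collected data says that "Table 2 provides a description of the variables, definitions and data sources used to create variables". Three rows of Table 2 matter here:

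- **Medications Prescribed** lists "VA Product name, strength, day supply, number of pills dispensed" for VA fills, and the National Drug Code for Medicare Part D.
- **Dose** carries the label "average monthly dose (dose per unit × day supply" (in parentheses). Its How defined cell reads "Generic, day supply, number of units, dose, Medicare Part D: NDC code".
- **Duration** is defined separately, as "Day supply summed over time".

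Table 3 lists "Long-term use/escalating dose of opioid medications" among the indicators of persistent morbidity. Its VA inputs are "VA Product, Dose, Day Supply". The row does not refer to the Table 2 expression and gives no rule for what counts as escalating.

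**The concern.** The Dose row names its target, an average monthly dose, and gives one expression for it. That expression does not produce the target. Strength per unit times days' supply ignores how many units are taken per day and grows with the length of the fill. It also disagrees with its own row, which lists number of units as an input but does not use it.

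The omission recurs in Table 3, where the VA inputs for the opioid indicator again leave out quantity. If Dose there is the Table 2 variable, the indicator inherits the expression. If it is the raw strength, escalation by more units per day cannot be recovered from the VA inputs listed.

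What is at stake is the dose-escalation part of one morbidity indicator. Under the third aim in the Analytic plan, having one or more such indicators is the exposure in the models for the Short Musculoskeletal Function Assessment and the other patient-reported outcomes.

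**Working it through.** The article reports no computed dose, so there is no figure to reproduce. The check is on the expression itself.

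**Notation.** S = dose per unit, Q = units dispensed, D = days' supply, q = Q ÷ D = units per day.

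**Formulas.**
- As printed in Table 2: S × D.
- Average 30-day dose: S × Q ÷ D × 30.
- Ratio of printed to average 30-day dose: D² ÷ (30 × Q) = D ÷ (30 × q). This equals 1 only when D = 30q, for example one unit a day for 30 days.

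**Illustrative fills.** The strengths and quantities are assumptions; none comes from the article.

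| Fill | S (mg) | Q | D | Printed: S × D | S × Q ÷ D × 30 | Ratio |
|---|---|---|---|---|---|---|
| 1/day, 30 days | 5 | 30 | 30 | 150 | 150 | 1.0 |
| 2/day, 30 days | 5 | 60 | 30 | 150 | 300 | 0.5 |
| 4/day, 30 days | 5 | 120 | 30 | 150 | 600 | 0.25 |
| 2/day, 90 days | 5 | 180 | 90 | 450 | 300 | 1.5 |
| 1/day, 90 days | 5 | 90 | 90 | 450 | 150 | 3.0 |
| 2/day, 15 days | 5 | 30 | 15 | 75 | 300 | 0.25 |
| 1/day, 30 days | 10 | 30 | 30 | 300 | 300 | 1.0 |

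**Reading the table.**
- *Missed escalation.* Going from 2 to 4 units a day leaves the printed value at 150, while the monthly dose doubles from 300 to 600 mg.
- *False escalation.* At 2 units a day, moving from a 30-day to a 90-day fill takes the printed value from 150 to 450, while the monthly dose stays at 300 mg.
- *Escalation that is caught.* At one unit a day for 30 days, moving from 5 mg to 10 mg takes both columns from 150 to 300.

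**More generous readings.**
- Suppose dose per unit means dose per day, or day supply means quantity supplied. The product is then the total dose of the fill, S × Q. At 2 units a day of 5 mg this is 300 for 30 days and 900 for 90 days, so a long fill still counts three times.
- Suppose instead that the word average implies dividing by the months covered. At 2 units a day of 5 mg, 150 ÷ 1 = 150 and 450 ÷ 3 = 150. The fill-length problem goes, but the result is still half the monthly dose of 300 mg, and a rise to 4 units a day is still invisible.

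Only both readings together give the intended quantity, and the article states neither.

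**The case against.** The expression stands in the label column, while the How defined cell of the same row lists number of units. In a condensed table, loose shorthand is at least as plausible as a plan to ignore quantity. That stands as an explanation of how the line arose. It does not make the printed expression correct, and it is the only expression given.

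A reader might infer that the opioid indicator is in fact miscalculated. The article does not support that. It shows no dose calculation, Table 3 does not cite the expression, and escalation is left undefined. Misclassification is conditional on the expression being applied as written to that indicator.

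A reader might also infer that escalating dose is a named outcome of the first aim. The Analytic plan names long-term opioid therapy there. Escalation reaches that aim only through the general reference to indicators of persistent morbidity. Long-term use can be built from summed day supply, which does not involve the expression.

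Nor is any shift shown in the functional-outcome comparison. Table 3 has 13 rows, and a single positive indicator is enough to be counted as exposed. A patient changes group only if escalation is the deciding item.

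**Conclusion.** The printed expression is wrong as a definition of average monthly dose. In the illustrative fills it gives between 0.25 and 3.0 times the 30-day dose, and it agrees only when day supply is 30 times the units per day. Applied fill by fill as written, it would miss escalation by more units per day and show escalation where only the fill length changed.

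The consequence for the study is bounded and conditional. It assumes that the Table 3 indicator uses the Table 2 Dose variable. On that assumption, the dose-escalation half of one of 13 indicators is misclassified and the long-term-use half is not. The any-indicator exposure in the third aim changes only for patients whose status turns on escalation alone. The article does not allow an estimate of how many that is.

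**What to change.** In Table 2, define average monthly dose as dose per unit × number of units ÷ day supply × 30. In Table 3, add number of units to the inputs of the opioid row and say that Dose there means the Table 2 variable, if that is the intention.

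The cost is a wording change in two table rows. For VA fills, Table 2 already lists the quantity dispensed. For Medicare Part D it lists only the National Drug Code, so availability of quantity and day supply should be confirmed before the definition is applied to those fills.

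Conversion to a common opioid equivalent, summing of concurrent fills and merging of overlapping fills are derivation details that can be settled elsewhere. The correction does not depend on them.
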